#### Cost-Effectiveness Study

The cost-effectiveness analysis will be performed in the population of randomized patients coming for a first genetic referral and for whom both GS strategies are performed in addition to the reference minimal strategy (i.e., 196 patients). The analysis will be based on the estimation of incremental cost-effectiveness ratios expressed in terms of cost per additional positive diagnosis. Deterministic analysis will take account of progress in technology. In order to manage the uncertainty associated with sampling, a non-parametric bootstrap analysis will be performed.

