Specifically, the primary objective of this study is to compare the percentage of causal genetic diagnosis identified by GS performed on a trio (the patient and both parents) (GST), to the use of the current French reference minimal strategy (Fragile X + CMA + 44GPS) in ID patients attending a first genetics consultation. Secondary objectives focus on the diagnostic yield, and include the following:• To compare the percentage of ID causal diagnosis identified by GST, to GS in the proband only (i.e., genome in solo, GSS) in a subgroup of randomized patients attending for a first genetic investigation. This evaluation is useful because in genetic counseling, both parents are not always available.• To describe the estimated additional diagnostic yield that would be obtained at each step in sequential analysis of the GS data: for the minimal 44GPS gene panel, the list of genes known to be associated with disease from OMIM (referred to simply as OMIM), and ES, in patients attending for a first investigation (never-explored patients) and in patients who have already undergone investigations (previously-explored patients).• To compare the percentage of causal diagnosis of ID identified by GST to that obtained with the French reference minimal strategy in various subgroups (defined according to age, severity of ID, presence of major non-cerebral manifestations or epilepsy), for patients with ID attending for a first genetic investigation (never-explored patients).• To compare the percentage of causal structural changes (CNV, balanced structural variants) identified by GST versus CMA.• The DEFIDAG study also aims to compare the reference strategy, GST and GSs, in terms of costs and effectiveness for the causal diagnosis of ID in patients with ID of unknown etiology, attending for a first genetic investigation.• Finally, three impact studies are planned. The first will estimate the costs associated with searching for a molecular diagnosis that could potentially be avoided by performing GS as the first line approach. The second will evaluate the impact on the frequency and type of medical, medico-social and psychological care in the year following the release of GS results, compared to care during the year prior to inclusion, in particular in patients who were already engaged in a diagnostic process prior to being invited to participate in the DEFIDIAG study. The third impact study will be performed in two centers, and will use a qualitative approach, namely interviews with a sample of parents, to explore: 1) the burden experienced by the parents, 2) emotional adjustment of the patient and the parents to the results of genetic tests, and 3) the patient and parents’ perception of the future.

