**FIGURE 1 F1:**
[figure not shown]
Impact study procedures and schedule (DEFIDIAG study). The figure represents the key timepoints for patient visits in the inclusion centers (inclusion in the study, delivery of results, 12-months post-delivery visit), which also correspond to the time of the interviews between either a sociology or psychology researcher and the parents/patients who agreed to participate in the qualitative impact study. The figure also shows the three periods considered for cost estimation (period 1: before inclusion; period 2: waiting for results; period 3: during the 12 months following the results) and, for each of these periods, the different elements collected from the care teams and families in order to have the examinations carried out (for the three periods) and those envisaged with each of the strategies to confirm the diagnosis (period 2).

**TABLE 1 T1:** Correspondence between objectives and target population (DEFIDIAG study).

Eligible index cases (*n* = 1,275)	
**Index cases with undiagnosed ID coming for the first time for a genetic investigation (*n* = 637)**	**Index cases with undiagnosed ID already investigated (*n* = 637)**
Primary objective: Compare the percentage of genetic causal diagnosis identified in ID patients by performing trio GS analysis vs. the use of the current French reference minimal strategy	
Secondary objective: diagnostic yields	
•Compare the percentage of ID causal diagnosis identified by GST vs. the reference strategy in different subgroups (defined according to age, or clinical manifestations)	
•Compare the percentage of causal structural changes identified by GST vs. chromosomal microarray analysis	
•Compare the percentage of ID causal diagnosis identified by GST vs. GSS in a subgroup of randomized patients (*n* = 196)	
Secondary objective: Describe the estimated additional diagnostic yield that would be obtained at different steps of sequential analysis, for the 44 gene panels, OMIM and exome analysis	
Secondary objective: Assessing the efficiency of the three strategies (the reference minimal strategy; GSs; GS_T_)	
	Secondary objective: Estimate the cost of the diagnostic odyssey that could be potentially avoided by first-line genomic analysis

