The strategy based on GST is expected to yield a diagnosis in at least 60% of patients with ID versus 30% with the reference minimal strategy in the population of patients attending for a first genetic investigation (never-explored patients). However, the strategies will be compared in 7 subgroups: 1) 3 defined by age: children <2 years old/2–5 years/>5 years; 2) 4 subgroups of patients defined according the severity of ID, and/or 3) with associated manifestations:1) mild ID associated with another sign, 2) moderate to severe ID, 3) ID with major non-cerebral abnormality, and 4) ID associated with epilepsy The smallest sub-group (subjects with mild ID associated with another significant sign) should represent around 15% of the total population, and the difference between the GST and the reference strategy in this particular subgroup can be assumed to be less than 15%. In addition, it is assumed that fewer than 1% of diagnoses identified with the referral minimal strategy will not be identified by the GST. Finally, we will also compare GST and GSS in a subgroup of randomized patients referred for the first time. For this specific comparison, a difference of 7% is expected, and <0.1% of diagnoses identified by GSS and not by GST. Considering these 9 planned comparisons (8 comparisons between GST and the reference strategy and 1 between GST and GS), the one-sided alpha risk is fixed at 0.00278. Based on these hypotheses, and a power of 80%, among patients seen for a first genetic investigation (50% of the population to be recruited), 41 patients are required for the main comparison, and 91 patients with mild ID + other syndrome are necessary. To recruit this number of patients, we estimate that it will be necessary to screen 607 patients attending for a first referral. A subgroup of 196 patients will be randomized to undergo GSS in addition to GST plus the reference minimal strategy. The sample size for this subgroup will be sufficient to compare GST and GSS in terms of diagnostic yield, as well as in terms of efficiency (a sample size over 150 is usually deemed sufficient). As we intend to include 50% of patients attending for a first genetics evaluation (never-explored patients), and 50% of patients who have already been investigated (previously-explored patients), a total of 1,214 patients are necessary. Considering that approximately 5% of samples will not be analyzable, it will therefore be necessary to include 1,275 index cases plus both their parents, for a total of 3,825 participants.

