#### Multidisciplinary Meeting

Each MDM includes clinician geneticists from the recruiting center, clinicians in charge of the patients’ follow-up (i.e., neuropediatricians, neurologists, pediatricians, etc.), molecular and chromosomal geneticists (from the reference laboratory and its mirror laboratory). To ensure a reasonable number of cases to be reviewed by each MDM, three independent MDMs are organized in parallel, each of them grouping two laboratories and four clinical centers. Each MDM will thus review about 400 inclusions. In order to ensure consistency in decision-making between MDMs, all positive cases from the three MDMs will be validated in a general DEFIDIAG study review meeting.

Each MDM is organized according to the following format: discussion of the list of variants of interest obtained by the simplex 44GPS analysis; then by GSS analysis (for the 196 randomized patients); and finally, by GST. At each step, additional confirmation analysis that would be required in the course of standard care (Sanger, qPCR, FISH, analysis on mRNA, etc.) is recorded on the MDM report and in the e-CRF, for further medico-economic evaluation. The final conclusion concerning the pathogenicity of variant(s) identified by the different approaches will be reached during the session and recorded in the e-CRF MDM conclusion. If additional confirmation methods are required, the reference laboratory will be in charge of this analysis and the case will subsequently be reviewed in a future MDM. The final results are recorded in a research report communicated to the clinical geneticist who included the index case.

Candidate genes or variations (new genes, or putative variations with no obvious pathogenic effect in known genes) are classified as class 3, of unknown significance until the end of the project. Potential reclassification will be managed using standard care procedures such as splice effect, epigenetic signature, functional studies, and cohorts of patients using international collaboration.

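### All cost-effectiveness ratios are confined to the 196 patients with solo genome analysis, but trio genome versus reference could also be estimated, more precisely, in about 607 never-explored patients

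*Protocol article*

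**What the plan says.** The Introduction states the efficiency objective as to "compare the reference strategy, GST and GSs, in terms of costs and effectiveness for the causal diagnosis of ID", in patients attending for a first genetic investigation. It also gives the cost-effectiveness of genome sequencing against the standard minimal protocol as an aim of the whole study. Ethics and Dissemination lists two gaps in French economic evidence: genome sequencing against the reference strategy, and trio against solo.

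The Cost-Effectiveness Study section sets the analysis population as randomized first-referral patients "for whom both GS strategies are performed in addition to the reference minimal strategy (i.e., 196 patients"), with incremental ratios per additional positive diagnosis and a non-parametric bootstrap. The number comes from Population: "A subgroup of 196 patients will be randomized to undergo GSS in addition to GST plus the reference minimal strategy". The only argument there about size for the economic question is that "a sample size over 150 is usually deemed sufficient".

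Study Setting says that each patient is their own control and undergoes both GST and the reference strategy. Statistical Analyses tests that pair in the whole first-investigation population. Population says that "it will be necessary to screen 607 patients attending for a first referral", and Table 1 lists "Index cases with undiagnosed ID coming for the first time for a genetic investigation (*n* = 637") to be included.

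On cost data, the Multidisciplinary Meeting section says that confirmatory testing at each step "is recorded on the MDM report and in the e-CRF, for further medico-economic evaluation"; only the GSS step is limited to the 196. Inclusion describes the family diary of service use without a subgroup limit. Medico-Economic Evaluation values GSS and GST by micro-costing and does not say in which patients.

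**The concern.** A patient needs a GSS result to contribute to GSS versus reference or to GST versus GSS. No GSS result is needed for GST versus reference, yet the restriction is applied to every ratio alike. About two thirds of the never-explored patients who have both results are therefore absent from the economic estimate of a contrast that the article says it wants for decisions on first-line use and tariffs.

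Two things are at stake. The ratio is less precise than the enrolled patients may allow. The economic analysis will also use a different incremental yield from the primary analysis, so the trial may report two GST-versus-reference gains that differ by sampling error alone.

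**Working it through.** **Where 607 and 196 come from.** The one-sided alpha is 0.025/9 = 0.00278, with 80% power.
- Never-explored: 91 patients in the smallest subgroup, at 15% of the population, gives 91/0.15 = 606.7, so 607. Doubled, this is 1,214; times 1.05 it is 1,275 (1,274.7 rounded up). These are the plan's figures.
- Solo subgroup: with a 7% difference and 0.1% reverse discordance (p10 = 0.07, p01 = 0.001), the simple McNemar formula (z_alpha + z_beta)² × (p10 + p01)/(p10 − p01)² gives 194.8, and the version with separate null and alternative variances gives 191.7. Both are close to 196. The number is thus explained by the GST-versus-GSS yield test, not by a precision target for a cost-effectiveness ratio.

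**Share left out of the economic analysis.** 607 − 196 = 411, and 411/607 = 67.7%. I take 607 as the analysable number. The article expects that "approximately 5% of samples will not be analyzable", and 637 × 0.95 = 605, so this makes no practical difference.

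**Precision of the incremental yield.** For a paired difference d = p10 − p01,

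SE = sqrt((p10 + p01 − d²)/N).

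The plan expects 60% versus 30%, so d = 0.30. It assumes that fewer than 1% of reference diagnoses are missed by GST. Read as 1% of the 30%, p01 = 0.003. Read as 1% of patients, p01 = 0.01, the value with which an exact McNemar calculation reproduces the plan's 41 and 91.

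| p01 | N | SE | 95% half-width |
|---|---|---|---|
| 0.003 | 196 | sqrt(0.216/196) = 0.0332 | 6.5 points |
| 0.003 | 607 | sqrt(0.216/607) = 0.0189 | 3.7 points |
| 0.01 | 196 | sqrt(0.230/196) = 0.0343 | 6.7 points |
| 0.01 | 607 | sqrt(0.230/607) = 0.0195 | 3.8 points |

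The width ratio is sqrt(607/196) = 1.76 under either reading. Equivalently, using 607 narrows the interval by 1 − sqrt(196/607) = 43%.

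**Effect on the ratio at a fixed incremental cost.** The ratio scales as 1/d, so its limits relative to the point value are 0.30/(0.30 ± half-width).
- p01 = 0.003: 0.82 to 1.28 with 196 (−18% to +28%); 0.89 to 1.14 with 607 (−11% to +14%).
- p01 = 0.01: 0.82 to 1.29 with 196; 0.89 to 1.15 with 607.
- If the true gain were only 0.15 (p01 = 0.01): 0.74 to 1.56 with 196; 0.83 to 1.26 with 607.

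**Possible gap between the two reported gains.** The 196 are nested in the 607, so the 95% range for the difference between the two yield estimates is 1.96 × sqrt(0.216 × (1/196 − 1/607)) = ±5.4 points.

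These figures carry sampling variation in yield only. The article gives no standard deviation for costs and no correlation between cost and yield.

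**The case against.** The strongest reply is that the planned evaluation compares three strategies. A joint incremental analysis with one within-patient bootstrap needs all three results, and only the 196 have them. On the plan's figures the yields are 30% (reference), 60 − 7 = 53% (GSS) and 60% (GST). If GSS is not dominated, the sequential ratios are GSS versus reference and GST versus GSS, and the other 411 patients cannot supply either directly. This stands: it justifies keeping the analysis in the 196 and argues against making a 607-patient ratio the main economic result. It does not explain why GST versus reference, a contrast that the article names in its own right, should be available only from the 196.

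Four stronger readings are tempting, and the document does not support them.
- A reader might infer bias. The 196 are randomized from never-explored patients, so the loss is of precision only.
- A reader might infer that the other patients' data are thrown away. They are used in the primary, subgroup and structural-variant comparisons and in the follow-up impact study; they are absent from the cost-effectiveness analysis only.
- A reader might infer that identical cost records exist for all never-explored patients. The diary and the meeting records are not described as limited to the 196, which makes this likely, but no section says it, and the patient set for micro-costing is not stated.
- A reader might infer that the economic conclusion would change. With 196 patients the gain is still about 23 to 37 points, well away from zero, and no decision threshold is given.

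**Conclusion.** The restriction to 196 is valid, and the three-strategy analysis needs it. For GST versus reference alone it is not needed, and it makes the interval for the incremental yield 1.76 times as wide: about ±6.5 to 6.7 points instead of ±3.7 to 3.8. The remark that more than 150 is usually enough sets no precision target and gives no reason to leave out available pairs.

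The size rests on the plan's 60% and 30% yields, on 607 analysable never-explored patients, and on incremental cost being held fixed. The gain in the ratio itself also depends on cost items being available outside the 196, which the article suggests but does not state. This is a cheap improvement in precision, not the correction of an error.

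**What to change.** Keep the three-strategy analysis with its joint bootstrap in the 196 as planned. Pre-specify, as a supplementary analysis, a GST-versus-reference ratio in all analysable never-explored patients, using the same bootstrap. Before doing so, confirm that the cost items (consultations, sampling, reference tests, confirmatory tests by strategy) are collected outside the 196. If micro-costing was done in only some patients, its result can be applied to the others as a unit cost.

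The change needs no new patients, only wording and analysis work. Its drawback is two GST-versus-reference ratios with different denominators. Each should be labelled with its population and role, and the 196-patient ratio can be read as a consistency check on the larger one.

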#### Impact Studies

The costs of finding a diagnosis will be described only in the population of patients who had previously had genetic investigations (50% of the 1,275 index cases), as the mean and standard deviation, if normally distributed, or as median and interquartile range otherwise.

The analysis of the impact of genomic analysis on medical, medico-social, rehabilitation and psychological follow-up after the results are made known, will be performed separately in the previously-explored population (50% of the 1,275 index cases) on the one hand, and in the population attending for a first genetics investigation on the other hand (never-explored patients). Frequencies of follow-up changes between the period prior to inclusion and the period following the results will be calculated with associated 95% confidence intervals. A global analysis will then be performed, regardless of the results of GST. Sub-analyses will be conducted according to the result of GST: positive, negative or uncertain.

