#### Secondary Outcomes

• Efficacy in terms of diagnostic yield: identification of causal structural changes• Efficiency: estimation of the incremental cost-effectiveness ratio, expressed in terms of cost per additional positive diagnosis.• Quantitative impact studies• Cost of the diagnostic odyssey: mean cost related to the iterative search for a diagnosis in the previously investigated population.• Change in follow-up: criteria will be the change in the number and type of medical, medico-social, rehabilitative, and psychological care induced by the results of the trio genomic analyses.• Qualitative impact studies: A sociologist and a clinical psychologist will explore the consequences on the family, and on the personal, professional and social life of the parents who take care of a child or an adult with ID, as well as the emotional adjustment and possible information overload for the parents at the various stages of the study (inclusion, results rendering, 12 months after receiving results).

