### Impact Studies

Two impact studies will be conducted: the cost of the diagnostic odyssey will first be estimated. It will include the cost of all diagnostic procedures from the first genetics consultation, to inclusion in the DEFIDIAG project (period 1 of Figure 1). The impact of genomic analyses on follow-up will also be assessed. It will be based on a before-after study (period 3 compared to period 1) and will include treatment and diet as well as rehabilitation, psychological and medico-social follow-up.

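### The diagnostic-odyssey outcome is defined as a mean cost, but the analysis rule replaces the mean with a median whenever costs are not normally distributed

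*Protocol article*

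**What the plan says.** Three parts of the protocol article bear on this cost.

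- **Outcome.** Secondary Outcomes defines it as the "mean cost related to the iterative search for a diagnosis in the previously investigated population".
- **Analysis.** The Impact Studies paragraph under Data Management and Data Analyses restricts the description to patients with earlier genetic investigations, half of the 1,275 index cases. It summarises their costs "as the mean and standard deviation, if normally distributed, or as median and interquartile range otherwise".
- **Purpose.** The Introduction wants to estimate the "costs associated with searching for a molecular diagnosis that could potentially be avoided by performing GS as the first line approach". Table 1 repeats this for the already-investigated group: "Estimate the cost of the diagnostic odyssey that could be potentially avoided by first-line genomic analysis".

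The Impact Studies paragraph that follows the Medico-Economic Evaluation sets out what is counted: "It will include the cost of all diagnostic procedures from the first genetics consultation, to inclusion in the DEFIDIAG project". The closing part of Ethics and Dissemination says that the cost-effectiveness and impact studies are expected to show savings.

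**The concern.** The outcome and its analysis rule name different statistics. Under the rule, the mean is reported only if the costs look normal. Otherwise the median takes its place, and no sentence says that the mean is still given. An analyst who follows the article exactly could finish without reporting the outcome it defines.

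A normality rule of this kind is a common habit for clinical measurements, where mean and median both serve as a typical value. For costs they answer different questions. The mean is what the health service spent per patient. The median is what the middle patient cost, and it takes no account of how expensive the longest searches were. In a study of the diagnostic odyssey, those long searches are much of what is of interest. If the costs are right-skewed, the reported figure would lie below the average spending that the objective concerns.

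**Working it through.** **1. The two statements side by side.**

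| | Secondary Outcomes | Impact Studies (analysis) |
|---|---|---|
| Quantity | cost of the search for a diagnosis | same |
| Population | previously investigated patients | same |
| Statistic | mean | mean if normal, median otherwise |

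Quantity and population agree; the statistic does not. This step needs no outside figure.

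**2. Group size.** Half of 1,275 is 0.5 × 1,275 = 637.5, which reproduces the 637 in Table 1. The article states no cost figure, so there is none to reproduce.

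**3. Which branch of the rule would apply.** The cost is a sum of procedures per patient. It cannot be negative, and it grows with the length and intensity of the search. Right skew is therefore plausible, but it is an assumption, because the article gives no mean, SD or distribution. It also names no normality test. As an illustration, 200 samples of 637 were simulated for each of several CVs from 0.3 to 2.0, once from a log-normal and once from a gamma distribution. Shapiro-Wilk at the 5% level rejected normality in every sample. This does not show that the real costs are skewed, since the samples were drawn from skewed distributions. It shows that at this sample size even modest skew would trigger the median.

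**4. Gap between median and mean.** For log-normal costs, σ² = ln(1 + CV²), so

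median / mean = exp(−σ²/2) = 1 / √(1 + CV²).

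- CV 0.5: 1/√1.25 = 0.894, median 11% below the mean
- CV 1.0: 1/√2 = 0.707, median 29% below
- CV 1.5: 1/√3.25 = 0.555, median 45% below

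For gamma costs with shape 1/CV², the median is 8%, 31% and 59% below the mean at the same CVs. Over the wider CV range of 0.3 to 2.0, the gap runs from 3% to 83% across the two distributions. The direction is the same under both. The size depends on the assumed CV and shape.

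**5. Is the mean too imprecise to report if costs are skewed?** The approximate 95% half-width relative to the mean is 1.96 × CV / √637, with √637 = 25.24.

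- CV 0.5: 3.9%
- CV 1.0: 7.8%
- CV 1.5: 11.6%
- CV 2.0: 15.5%

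At each of CV 0.5, 1.0 and 1.5 the half-width is well below the log-normal gap in step 4 (3.9% against 11%, 7.8% against 29%, 11.6% against 45%). Skew of this degree is no reason to give up the mean.

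**The case against.** The strongest reply is that this is one descriptive secondary outcome. Patient-level costs are collected whatever summary is printed, so the mean can always be computed. The article also plans neither a total nor a direct comparison with the price of sequencing for this figure. All of that is correct and limits the consequence. It does not remove the mismatch: the outcome is defined as a mean, and the stated rule can leave the mean out.

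A reader might infer more than the article supports:

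- **That the median will certainly be reported and will understate the cost.** This depends on right skew, which is plausible but not documented.
- **That the sequencing tariff would be set too low.** The article ties the tariff to the complete cost of genome sequencing, and values the sequencing strategies by micro-costing. The odyssey cost covers the time before inclusion and does not enter that calculation.
- **That pooling all previously investigated patients is an error.** Secondary Outcomes defines the outcome in exactly that population.
- **That costs were avoidable only in patients in whom trio sequencing is positive.** The Introduction presents genome sequencing as a possible replacement for microarray and other sequencing. Tests that it replaces could be avoided whatever its result.
- **That the lack of a stated confidence interval is itself a fault.** An article commonly leaves this to the full protocol or SAP. The interval belongs in the remedy and is not a separate finding.

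**Conclusion.** The inconsistency stands: same cost, same patients, and an analysis rule that can discard the statistic by which the outcome is defined. This rests on the article's own wording and can be held with high confidence.

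The understatement is conditional. If costs are right-skewed, the rule would very likely lead to the median at about 637 patients. Under a log-normal shape the figure would then be about 11% to 45% below the mean for CVs of 0.5 to 1.5; both the shape and the CVs are assumptions. The point is worth correcting because the objective concerns avoidable cost and the impact studies are expected to show savings. It changes no hypothesis test, sample size, primary result, incremental cost-effectiveness ratio or tariff calculation.

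**What to change.** In the Impact Studies paragraph under Data Analyses, replace the normality rule for costs with a sentence to this effect: the arithmetic mean cost per patient is reported whatever the distribution, with a 95% confidence interval (for example by non-parametric bootstrap), and the median and interquartile range are given as additional description only.

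This brings the analysis into line with Secondary Outcomes. The bootstrap is already planned for the cost-effectiveness analysis of the 196 randomised patients and can be applied here. The cost is one sentence and a short extra computation, with no new data and no change in study conduct.
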